#### Ecological Momentary Assessment

The same set of EMA questions is provided at all prompts: (1) 10 questions of the *Positive and Negative Affect Schedule for Children* [92] measure positive affect (happy, cheerful, proud, joyful, and lively) and negative affect (sad, scared, miserable, afraid, and mad). The Positive and Negative Affect Schedule for Children has been used in a diary study and showed good psychometric properties in intensive longitudinal designs [93]. (2) The *Social Phobia Weekly Summary Scale* [94] assesses maintaining factors of social anxiety. Six items rated on a 9-point Likert scale from 0 to 8 evaluate the extent of social anxiety, social avoidance, self-focused versus external attention, pre-event, and postevent processing. All items were adapted to reflect the time frame of the EMA measurement (ie, “Since the last prompt”) and the language of the target group. To assess all maintaining mechanisms of social anxiety suggested in the Cognitive Model by Clark and Wells [24] and based on similar existing items [95], we formulated 2 additional items to evaluate automatic thought processing and level of self-confidence in social situations: “In social situations, I have had many negative automatic thoughts running through my head” and “Since the last prompt, I have had little confidence in myself.” Both items are rated on a 9-point Likert scale accordingly. (3) *Momentary social context* is assessed by 4 questions based on similar EMA items from a repository [95]; initially, participants indicate in which social situation they currently are: alone, family, close friends, boyfriend or girlfriend, colleagues, known persons, or strangers. Depending on their answer, they are asked if they would prefer to be alone or with someone (yes or no). Additionally, they indicate if they are currently in contact with others online (yes or no). Finally, they rate their experienced pleasantness in the current situation on a visual analog scale from not at all (0) to extremely (100).

#### Guardian Assessment

Guardians who provide their email addresses on the consent form voluntarily are assessed at baseline, midintervention, postintervention, and follow-up. In all assessments, they rate their child’s social anxiety using the *Parents’ Questionnaire on Social Anxieties in Childhood and Adolescence* (German: Elternfragebogen zu sozialen Ängsten im Kindes und Jugendalter) [96]. In 18 items, statements about the adolescent’s behaviors and fears are rated on a 4-point Likert scale from not at all (0) to very much (3). Furthermore, guardians provide demographic data and answer questions about their child’s treatment motivation and expectations during the baseline assessment. The *Motivation for Youth's Treatment Scale* [86] assesses guardians’ motivation for treatment with 8 items rated on a 5-point Likert scale from do not agree at all (–2) to agree completely (2). The *Credibility or Expectancy Questionnaire—Parent Version* [97] measures guardians’ expectations of the online intervention using 6 items. In total, 4 items are rated on a scale from not at all (1) to very (9), and 2 items on a scale from 0 to 100%.

### Study Group Condition

#### SOPHIE Intervention

The internet-delivered self-help intervention SOPHIE (see Table 2) has a duration of 8 weeks and is based on the Cognitive Model by Clark and Wells [24] adapted to specific needs of adolescents [47] and existing evidence-based online interventions for adults with SAD [98-104]. The first version of the SOPHIE intervention was tested on 46 healthy adolescents. Based on their feedback, we improved the usability and understandability. An introductory module familiarizes adolescents with the intervention. Successively, 6 modules cover the maintaining mechanisms of the Cognitive Model and instruct adolescents to apply the learned strategies in exposure exercises in everyday life. The last module contains a short repetition and summary. The structure of each module includes a review of the previous module, an introduction to the current module’s content, a summary at the end, and a quiz. Content is provided by animated video inputs, short text explanations, and exercises.

To enhance adherence and motivation throughout the intervention, adolescents receive guidance from e-coaches who provide weekly personalized support via a secured text-based messaging system. They summarize completed exercises, provide a preview of upcoming modules, send reminders to use the intervention, answer questions, and motivate participants by relating exercises to their personal goals. e-Coaches are psychology graduate students who were trained by the first or last author in offering guidance. Before sending, each guidance message is additionally peer-reviewed by another e-coach.

**Table 2 table2:** Description of all modules of the SOPHIE program^a^.

Module	Image	Content
(1) Introduction	[figure not shown]	A user guide explains the structure and different elements of the online intervention. Participants are introduced to the 2 protagonists, Sophie and Leon, and can choose their avatar. They learn what social anxiety is, in which situations they may arise, and *set their personal goals* for the online intervention. Additionally, they are introduced to a progressive muscle relaxation exercise and are instructed to do this exercise daily.
(2) Emergence and maintenance of social anxiety	[figure not shown]	Participants learn about *etiological and maintaining factors of social anxiety*. In an exercise, they write down their personal anxiety cycle. For the following week, they are instructed to observe their social anxiety symptoms and enter their observations in their logbook.
(3) Automatic thoughts	[figure not shown]	Participants are introduced to *automatic thoughts* and their importance in maintaining social anxiety. In 2 exercises, they are instructed on how to recognize and modify their negative automatic thoughts. An additional relaxation exercise “safe place” is introduced to support their daily relaxation practice.
(4) Self-image	[figure not shown]	Participants learn about *self and other perspective* of a person, reasons for a positive self-image as well as possible consequences of a negative self-image. During an exercise, they are instructed to reflect on their assumptions of themselves, to recognize both negative and positive sides thereof, and to find a good balance. Participants learn 3 strategies to positively improve their self-image.
(5) Self-focused attention	[figure not shown]	Participants discover *self-focused attention* and the reinforcing impact it has on social anxiety. In an exercise, they train to shift their attention. In front of a virtual audience, they must tell a story and are instructed to focus their attention on the situation instead of themselves. They are introduced to a new relaxation exercise “relaxing world” to complement their relaxation practice.
(6) Reality tests I	[figure not shown]	Participants are introduced to reality tests (*exposure exercises*). To prepare for their own reality tests, participants establish their fear hierarchy. In the upcoming week, they conduct their reality tests and record the level of anxiety before and after.
(7) Reality tests II	[figure not shown]	Participants learn about strategies to deal with possible difficulties in reality tasks. Further, they are introduced to *socially competent behavior*. Thereby, examples of competent behavior are contrasted with examples of insecure behavior in social situations. Participants are instructed to continue with their reality tests.
(8) Repetition	[figure not shown]	The last module summarizes the content of the online intervention and participants reflect on their personal goals. They record a video of themselves in which they explain what social anxiety is, how they experience it, and how they learnt to cope with it. Later, they can replay this video to remind themselves of their progress.

^a^Displayed pictures were generated with the video program Vyond [105].

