### Procedures

Adolescents interested to take part in the study leave their email addresses on the study website [60]. They receive the participant study information by email and are asked to provide informed consent or assent (see Figure 1 for study flow). Participants younger than 14 years provide written assent, and their parent or guardian provides written consent. Participants 14 years or older provide consent on their own. Informed consents are accepted both on paper by mail and electronically as scans via email. Once the consent forms have been received, they are printed out and stored in analog form. Afterward, potential participants are screened for eligibility. Those with a score lower than 16 on the Social Phobia Inventory (SPIN) [61,62] are not included in the study but receive immediate access to the online intervention. The cutoff of 16 was chosen in reference to a previous study that showed good discrimination between healthy and subclinical adolescents [63]. Adolescents with a SPIN score of 16 or higher receive the remaining baseline questionnaires. Subsequently, they are interviewed by trained psychology graduate students via phone to ascertain whether they fulfill the diagnostic criteria for SAD or not. Those with a current diagnosis of SAD are assigned to the SAD group, while those with no current and no past SAD diagnosis are assigned to the subclinical social anxiety group. Training and weekly supervision of the graduate students are carried out by the first and last authors.

Participants are assigned to the intervention group or the control group by stratified block randomization to ensure that both groups are balanced regarding the diagnostic status: SAD or subclinical social anxiety. The randomization is carried out after all data collected by the diagnostic interview including diagnoses are entered into the electronic protocol form hosted on Qualtrics (Qualtrics XM) [64]. Randomization was set up before the start of the study by the first author (ie, number of groups, allocation ratio [1:1], and size of blocks). During the study, the allocation list was produced using an automated computer-generated random numbers table and was concealed from the investigators and the participants. After randomization, the intervention group receives immediate access to the online intervention.

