#### Care-as-Usual Group

Participants randomized to the CAU group are only contacted for assessments and receive access to the online intervention after follow-up. They are free to take advantage of any other health service. To account for additional help, the use of assistance is assessed post intervention and follow-up (details in Table 1).

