#### Main Analyses

The primary outcome, that is, change in social anxiety, will be tested using Linear Mixed Effects Models. Time (baseline, midintervention, post intervention, and follow-up), intervention condition (SOPHIE and CAU), diagnostic status (SAD and subclinical social anxiety), and interactions (time*intervention condition; time*diagnostic status; intervention condition*diagnostic status; time*intervention condition*diagnostic status) will be specified as fixed effects, baseline SPIN value will be added as a fixed covariate and participant as a random effect to allow for between-person variation.

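### Only the SOPHIE arm has e-coaches, but the stated primary model names only a participant random effect, so it makes no allowance for possible e-coach clustering in that arm

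*Protocol article*

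**What the plan says.** The section SOPHIE Intervention describes a self-help program with human guidance: "adolescents receive guidance from e-coaches who provide weekly personalized support via a secured text-based messaging system". The coaches are students trained by the same one or two people ("e-Coaches are psychology graduate students who were trained by the first or last author in offering guidance"), and before sending, "each guidance message is additionally peer-reviewed by another e-coach". The Care-as-Usual Group section gives the comparison arm no coach during the trial: "Participants randomized to the CAU group are only contacted for assessments and receive access to the online intervention after follow-up".

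Under Main Analyses, the primary outcome "will be tested using Linear Mixed Effects Models". The fixed effects are time, condition, diagnostic status, their interactions and baseline SPIN. The random part is "participant as a random effect to allow for between-person variation". Further Analyses carries this model over to the secondary outcomes. Sample Size uses a repeated-measures ANOVA calculation and mentions no clustering.

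The article does not say how many e-coaches there are, how they are assigned, how many participants each has, or whether a participant keeps the same coach.

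**The concern.** Guidance is a designed part of the intervention, and the article expects it to matter. The Introduction cites evidence that human support helps adherence and effect, and names alliance and adherence among the influences on the intervention effect. Table 1 measures alliance at weeks 2, 4, 6 and 8, and Mediation Analyses models both as mediators. If some coaches obtain better results than others, participants who share a coach have correlated outcomes. This can happen in one arm only, so the data would be partially nested.

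A model with only a participant random effect sets the between-coach variance to zero. If that variance is positive, the model understates the standard error of the SOPHIE-CAU contrast, its confidence interval is too narrow, and its test rejects too often. The planned model also cannot show whether the coach variance was negligible.

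**Working it through.** **The plan's own figure.** The stated group sizes can be reproduced without any clustering term. Inputs from Study Design and Sample Size: d = 0.35 (SAD) and 0.20 (subclinical), alpha 5%, power 80%, r = 0.4, 4 measurements, 2 arms. For the within-between interaction in a repeated-measures ANOVA, f = d/2, lambda = N × 4 × f² / (1 − r), df1 = 3 and df2 = 3(N − 2).

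- SAD: f = 0.175, N = 56, lambda = 56 × 4 × 0.030625 / 0.6 = 11.43, power 0.810.
- Subclinical: f = 0.10, N = 166, lambda = 166 × 4 × 0.01 / 0.6 = 11.07, power 0.803.

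So 56 and 166 reproduce exactly with no design effect.

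**Effect of coach clustering, if present.** With 1:1 allocation, 222 / 2 = 111 participants are in SOPHIE. The number of coaches K and the ICC are assumptions.

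- Caseload: m = 111 / K.
- Design effect in the SOPHIE arm: DE = 1 + (m − 1) × ICC.
- Variance factor for the contrast of two equal arms, one of them clustered: V = (DE + 1) / 2.
- True alpha: 2 × [1 − Phi(1.96 / √V)].

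| K | m | ICC | DE | V | SE factor √V | True alpha |
|---|---|---|---|---|---|---|
| 20 | 5.55 | 0.01 | 1.046 | 1.023 | 1.011 | 5.3% |
| 10 | 11.1 | 0.01 | 1.101 | 1.051 | 1.025 | 5.6% |
| 6 | 18.5 | 0.01 | 1.175 | 1.088 | 1.043 | 6.0% |
| 20 | 5.55 | 0.05 | 1.228 | 1.114 | 1.055 | 6.3% |
| 10 | 11.1 | 0.05 | 1.505 | 1.253 | 1.119 | 8.0% |
| 6 | 18.5 | 0.05 | 1.875 | 1.438 | 1.199 | 10.2% |

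At ICC 0, every row returns 5.0%. The figures use a normal approximation, equal caseloads and one coach per participant.

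**By diagnostic group, 10 coaches.** The trial is powered in each group separately, and caseloads within a group are smaller.

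- SAD, 28 in SOPHIE: true alpha 5.1% at ICC 0.01 and 5.5% at ICC 0.05; power falls from 0.810 to 0.806 and 0.791.
- Subclinical, 83 in SOPHIE: true alpha 5.4% and 7.1%; power falls from 0.803 to 0.787 and 0.726.

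**Which coach term repairs the standard error.** Main Analyses keeps baseline as a level of time, so the effect on change is the time-by-condition contrast. Take 110 per arm, 10 coaches, unit variance, within-person correlation 0.4, and a coach variance of 0.05 that arises only after baseline.

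- Variance of one participant's change from baseline to post: 2 × (1 − 0.4) = 1.2.
- Model SE without a coach term: √(2 × 1.2 / 110) = 0.1477.
- Model SE with a coach intercept constant over time: still 0.1477, because the intercept enters baseline and post equally and drops out of the change.
- True SE: √(2 × 1.2 / 110 + 0.05 / 10) = √(0.02182 + 0.005) = 0.1638.
- Model SE with a coach effect at post-baseline visits only: 0.1638.

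**The case against.** The strongest reply is that nothing in the article shows coach clustering exists. SOPHIE is a self-help program with eight standard modules, the coaches share their training, support is by text, and a second coach checks each message. All of this points to a small ICC. Clean nesting under one main coach is also an assumption, and alliance is rated by each participant, so measuring it does not show that coaches differ. This stands, and the point is therefore conditional. A reader might infer that SOPHIE outcomes are clustered and that the standard error is too small as a matter of fact. The documents do not support that, because they give no ICC, number of coaches or assignment rule.

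Second, participants are individually randomized. If SOPHIE changed nobody's outcome, its coaches would not either, and no inflation would arise. The alpha figures apply to a null in which coach effects differ but average zero, with the coaches seen as a sample of possible coaches. Conditional on the coaches actually used, the participant-level standard error is a defensible target. This also stands. A reader might further infer that the result could not generalise beyond these coaches, but that is a choice of inference target and not an error in the plan.

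Third, this is a condensed article, the analysis plan is not shown, and the text does not say that participant is the only random effect. That limits the weight of the point but does not remove it. The article sets out the primary model term by term and names one random effect. If the full plan already contains a coach term, the point is answered.

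**Conclusion.** The point holds in conditional form. Coaching exists in one arm only, and the stated model makes no allowance for variation between coaches. The standard error of the SOPHIE-CAU contrast would be too small if the coach ICC is above zero and participants mostly keep one coach.

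The size is unknown. Over the assumed range it runs from trivial (SE understated by about 1%, alpha 5.3%, with 20 coaches and ICC 0.01) to material (SE understated by a factor of 1.20, alpha 10.2%, with 6 coaches and ICC 0.05). The features of the guidance favour the lower end. They do not justify fixing the coach variance at zero unchecked, given that the trial itself expects alliance and adherence to shape the effect.

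**What to change.** Derive each SOPHIE participant's main e-coach from the messaging system. Add to Main Analyses and Further Analyses, at least as a prespecified sensitivity analysis, a partially nested term: a random e-coach effect that acts only in the SOPHIE arm and only at post-baseline visits (coach by post-baseline time). CAU participants carry no coach effect. Use small-sample degrees of freedom, for example Kenward-Roger, since the coaches may be few. Do not use a time-constant coach intercept, which leaves the time-by-condition standard error unchanged and gives coaches influence at baseline, before guidance begins.

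Report the number of coaches, how they were assigned, how often participants changed coach, and the estimated coach variance or ICC.

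The cost is one derived variable, one random term and possibly slightly wider intervals. If the coach variance is estimated near zero, the estimate and its standard error stay essentially as planned, though the degrees of freedom may differ because the article names no method for them. No design, recruitment or treatment procedure changes. The Results section reports 106 enrolled by April 2023 and first results expected in 2024, so on the article's timeline the addition could be made before analysis.

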#### Care-as-Usual Group

Participants randomized to the CAU group are only contacted for assessments and receive access to the online intervention after follow-up. They are free to take advantage of any other health service. To account for additional help, the use of assistance is assessed post intervention and follow-up (details in Table 1).

### Project and Risk Management

In weekly monitoring procedures, project implementation, clinical (eg, study withdrawals and adverse events), and research integrity (eg, blindness, data safety, important harms, or unintended effects) are ensured. Potential risks to participants are minimal. However, there is a potential inconvenience as filling out the questionnaires and the online intervention requires time.

In the case of suicidality (assessed at every assessment point by item 9 of the Patient Health Questionnaire [81]), a predefined suicidality protocol is applied; participants immediately receive an email with numbers for psychiatric services. Additionally, a member of the study team contacts the participant on the following working day to clarify acute suicidality. If acute suicidality is present, we offer additional help for instance by providing contact details on mental health services near to the adolescent’s home, if necessary, we support the referral to an appropriate service and decide on the continuation in the study. All participants must provide a safety contact in case that we cannot reach the adolescent who triggered the suicidality protocol.

Adverse events, all untoward events in a participant, including events not necessarily caused by or related to the online intervention, are monitored from randomization to follow-up 5 months after randomization. All adverse events are reported to the principal investigator, the ethics committee, and are documented in the participant’s case report form.

### Data Management and Monitoring

All data are collected electronically except for informed consent and case report forms. Electronic data from all servers are extracted monthly and saved on a secure server of the University of Bern. All data are deidentified by removing names, email addresses, and location information, and are only accessible to the core study team as well as the head of research management for auditing purposes. Personal information is password-protected and stored in a secure electronic vault, separately from outcome data. All data will be stored for 15 years after the termination of the study. The research management of the Faculty of Human Sciences of the University of Bern supervises data collection and storage in quarterly meetings.

All participants create password-protected accounts for the online intervention and are allocated a unique identification number. The online intervention is hosted on a secure platform of the University of Bern. All questionnaire and interview data are recorded via Qualtrics [64]. Qualtrics uses the same unique identification number. Thus, no personal data are entered in Qualtrics. EMA data are assessed with the SEMA^3^ app and saved on a server of the University of Melbourne [65]. SEMA^3^ requires personal data only to send out invitations and deletes them immediately afterward. For identification, participants are allocated a SEMA^3^ numeric identification code.

### Plan of Analysis

All analyses will follow the intention-to-treat approach. Patterns of missing data in the Growth Mixture Models will be analyzed, and in case of “missing at random” or “missing completely at random,” multiple imputation will be applied.

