## Methods

### Study Design

This randomized controlled trial (RCT) investigates the efficacy of the online intervention SOPHIE for adolescents with subclinical social anxiety or a diagnosis of SAD. SOPHIE is compared to a CAU control condition in a 2×2×4 design with a 2-level between-subjects factor (2 experimental conditions: SOPHIE vs CAU), a 2-level between-subjects factor (2 diagnostic conditions: SAD vs subclinical social anxiety), and a 4-level within-subjects factor (repeated measures: baseline, midintervention at week 4, post intervention at week 8, and follow-up 5 months after randomization, ie, 3-months follow-up). All participants are additionally assessed in EMA surveys during the first 8 weeks (from baseline to postassessment) and for 2 weeks after follow-up assessment. Participants in the intervention group have additional process assessments at weeks 2 and 6 during the intervention.

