#### Further Analyses

Secondary outcomes (ie, global functioning, general anxiety symptoms, depressive symptoms, quality of life, self-esteem, and guardians’ rating of their child’s social anxiety) will be analyzed using Linear Mixed Effects Model as described earlier. In further analyses, therapy expectancy, therapy motivation (both adolescents’ and guardians’), and satisfaction with the intervention will be added as moderators. Categorical outcomes (eg, diagnostic status) will be analyzed using General Linear Mixed Effect Models with intervention condition, diagnostic status, and time course as fixed effects and participants as random effect. Additionally, Growth Mixture Modeling will be used to identify subpopulations with comparable growth trajectories of social anxiety and secondary outcomes over time (latent classes) and to identify predictors of these classes.

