#### Sample Size

The sample size of 222 was determined in 2 a priori power analyses for the primary research question using G*Power [106] based on an intention-to-treat approach to account for possible dropouts and repeated measures ANOVA. In the SAD group, we expected a small to moderate effect size (Cohen *d*=0.35) [18,107], and for the group with subclinical anxiety, a small effect size (Cohen *d*=0.20) [38,108-110]. For both groups, we assumed an α level of 5%, power of 80%, and a correlation between measurements of *r*=0.4. Consequently, the SAD group should consist of 56 participants, and the subclinical social anxiety group of 166 participants.

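### Multiple imputation is the named missing-data method for the growth mixture models; under the usual one-population imputation model it blurs the latent classes, and full-information likelihood is a cheap improvement

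*Protocol article*

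**What the plan says.** The missing-data paragraph opens Plan of Analysis in the Protocol article. It states that "Patterns of missing data in the Growth Mixture Models will be analyzed" and that, where missingness is judged at random or completely at random, "multiple imputation will be applied". Growth mixture models are the only model family the paragraph names. It does not describe the imputation model and does not mention full-information likelihood.

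Further Analyses gives the purpose of these models: to sort participants into latent classes by their course on social anxiety and the secondary outcomes, "and to identify predictors of these classes". They are an additional analysis. Under Main Analyses, "The primary outcome, that is, change in social anxiety, will be tested using Linear Mixed Effects Models".

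**The concern.** Class membership is unknown when the data are imputed. A standard imputation model therefore predicts a missing post or follow-up score from observed scores as if all participants came from one population. That contradicts the hypothesis the mixture model examines. An improver who leaves early is given values drawn towards the common course, and so is a non-improver, so the space between the classes fills up.

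There is a second, practical difficulty. Each imputed data set is fitted separately, and the number of classes and their labels can differ between data sets. Class shares and predictor effects are then harder to combine.

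What is at stake is whether real subgroups of course are found and how distinct they look. The Discussion presents learning which adolescents benefit most as one of the trial's contributions, and this analysis serves that aim. Under the missing-at-random assumption the plan already makes, the mixture likelihood can use incomplete records directly, so imputation is an extra step.

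**Working it through.** **1. The plan's own figure.** The missing-data paragraph gives none. The only figure used here is the sample size: "the SAD group should consist of 56 participants, and the subclinical social anxiety group of 166 participants", so 56 + 166 = 222. It reproduces as a repeated measures ANOVA, within-between interaction, with λ = f²·N·m/(1−r), f = d/2, r = 0.4 and m = 4 (taken from the four assessments in Study Design).
- SAD, d = 0.35: λ = 0.175² × 56 × 4/0.6 = 11.43, F(3, 162), power 0.810.
- Subclinical, d = 0.20: λ = 0.10² × 166 × 4/0.6 = 11.07, F(3, 492), power 0.803.

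The point does not depend on this calculation; 222 only sets the size of the simulation.

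**2. Assumed scenario.** The documents give neither an expected missing rate nor a class structure, so these are assumptions:
- 35% improvers; mean scores at the four assessments 36, 26, 16, 16 for improvers and 36, 35, 34, 34 for the others. The class differences are 0, 9, 18, 18.
- Random-intercept SD 7 and residual SD 5, so within-class variance is 49 + 25 = 74 and within-class covariance is 49.
- Monotone dropout after week 4 or week 8, depending on the last observed score (missing at random).

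**3. Mechanism by hand.** A one-population model uses pooled covariances: within-class covariance + 0.35 × 0.65 × (product of class differences).
- Var(week 4) = 74 + 0.2275 × 81 = 92.43. Cov(week 4, follow-up) = 49 + 0.2275 × 9 × 18 = 85.86. Baseline has variance 74 and covariance 49 with each later visit.
- Regressing follow-up on baseline and week 4 gives a week-4 slope of (74 × 85.86 − 49²)/(74 × 92.43 − 49²) = 0.89.
- Someone who leaves after week 4 is therefore imputed with an expected class difference at follow-up of 0.89 × 9 = 8.0, where the truth is 18.
- With week 8 also observed, the slopes on weeks 4 and 8 are 0.329 and 0.631, giving 0.329 × 9 + 0.631 × 18 = 14.3.

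This ignores the dependence of dropout on the last score. It shows why the imputed values lie between the classes.

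**4. Simulation.** The two-class mixture was fitted by EM, started from the true values, to the complete data, to the incomplete data by full-information maximum likelihood (FIML), and to 10 data sets imputed from one multivariate normal population (MI). There were 25 runs at n = 222. Detection means that BIC favours two classes over one.

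| Missing at follow-up | Class difference (true 18): FIML / MI | Within-class variance (true 74): FIML / MI | Correctly classified: FIML / MI | Two classes detected: complete / FIML / MI |
|---|---|---|---|---|
| 18% | 18.1 / 17.6 | 74 / 80 | 94% / 92% | 100% / 100% / 80% |
| 33% | 18.1 / 17.0 | 74 / 86 | 91% / 89% | 96% / 84% / 48% |
| 48% | 17.9 / 16.1 | 80 / 96 | 89% / 85% | 100% / 76% / 32% |

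Shrinkage under MI at n = 222: (18 − 17.56)/18 = 2.4%, (18 − 16.96)/18 = 5.8% and (18 − 16.10)/18 = 10.6%. Variance inflation: 80.4/74, 86.1/74 and 96.2/74, or 9%, 16% and 30%.

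**5. Bias or noise?** At n = 2000 (6 runs) FIML gives 18.0, 18.0 and 18.2, and MI gives 17.51, 16.86 and 16.43, a shrinkage of 2.7%, 6.3% and 8.7%. At the lowest missing rate the shortfall of 0.49 compares with a simulation standard error of 0.27/√6 = 0.11. The shortfall does not vanish with sample size, so it is bias.

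**6. Smaller separation.** With a true difference of 12, n = 2000 shows the same pattern (FIML 12.4, 12.7, 12.2; MI 11.9, 11.4, 10.6). At n = 222, however, BIC finds two classes in only 0-4% of runs by any method, complete data included.

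**7. A second design.** With 25% responders, means at post of 8 and 28, missing 29% at post and 35% at follow-up, N = 222, 5 imputations and 100 runs, detection is 90% (complete), 69% (FIML) and 31% (MI). The responder mean is 8.3, 9.0 and 10.6, and the responder share 26%, 28% and 30%. In a less separated setting (30 runs), detection is 37%, 10% and 2%.

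**The case against.** The strongest objection is that the harm needs a one-population imputation model, and the article does not say that one will be used. The detail may sit in an analysis plan that is not shown, and a class-aware imputation would avoid the problem. This stands in part. A reader might infer that the missing-data plan is shown to be wrong; the document does not support that, and the point is a conditional risk. It survives because the article names a method, that method's default is the one-population model, and the remedy replaces the named method without asking for missing detail. Adding correlated auxiliary measures to the imputation did not rescue class detection when tried.

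Three other strong readings fail:
- *Results from imputed data sets cannot be pooled.* They can, for example by fixing the number of classes and ordering them by trajectory. Pooling is harder, not impossible.
- *The protocol itself expects high dropout.* The Introduction attaches high dropout to one cited trial. Its general remark concerns poor engagement with online programmes, which is not the same as missed assessments. Procedures describes repeated reminders, and no missing rate is given.
- *The trial's efficacy result is at risk.* The primary test is a separate mixed model.

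It is also fair to say that the gain in detection depends on widely separated classes. A difference of 18-20 points is large on a scale with a maximum of 17 × 4 = 68. Even then the estimates move modestly (responder mean 9.0 against 10.6), and full-information likelihood itself loses precision as data go missing: correct classification falls from about 95% with complete data to 89% at 48% missing.

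**Conclusion.** The point holds as a cheap improvement to a further analysis. If the imputation model is the usual one-population model, multiple imputation works against the purpose of the growth mixture models. Class differences shrink by a few per cent at low missingness and by about a tenth when nearly half the follow-up scores are missing. Within-class variance rises by about 8-30%, and two classes are found clearly less often when they are far apart. Full-information likelihood avoids the systematic shrinkage under the same assumption.

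This rests on assumed dropout and class separation, a correctly specified mixture, data missing at random, and few simulation runs. The direction was the same in every design tried; the sizes are illustrative. If the classes are only about 12 points apart, the choice hardly affects detection at N=222, because no method finds them.

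**What to change.** In Plan of Analysis, replace the imputation sentence for these models with one stating that the growth mixture models will be fitted by full-information maximum likelihood under missing at random, with baseline predictors of dropout as covariates. If imputation is kept for these models, state that a class-aware (mixture) imputation model will be used.

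The cost is one sentence, and the likelihood route is less work than imputing and combining. The small downside is that auxiliary variables must enter the model as covariates and can no longer sit only in the imputation step.
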